## Abstract

**Background:**

Light-emitting diodes (LED) have been used to minimize muscle fatigue in athletes and healthy subjects. Patients with chronic obstructive pulmonary disease (COPD) are susceptible to early muscle fatigue.

**Objective:**

The objective of this study is to investigate the acute effects of LED on muscle function, exercise capacity and cardiorespiratory responses during isometric and dynamic exercise in patients with COPD.

**Methods:**

This study will assess 30 patients with moderate to severe obstruction (forced expiratory volume-one second,FEV_1_ ≤70% predicted). Isometric and dynamic protocols will be conducted in two visits each, for a total of four visits a week apart. First, venous blood will be taken from the patients. The isometric protocol will start with the determination of the maximum voluntary isometric contraction (MIVC) to determine the workload (60% of MIVC) for the isometric endurance test (IET). Patients will be randomized to receive either the placebo or LED application (each point will be irradiated for 30 s and the energy received at each point will be 41.7 J). Immediately after finishing this procedure, the patients will carry out the IET until the limit of tolerance or until a 20% fall of strength is observed. After the test, another blood draw will be taken. In another visit (one week later), the same order of procedures will be performed, except with the opposite (LED or placebo). For the dynamic endurance test (DET), the same procedures described above will be followed, except with 75% of the maximal workload obtained from the incremental cycle ergometer test used instead of the IET. The electromyography will be recorded during the isometric and dynamic protocols. Differences in muscle function, exercise capacity and cardiorespiratory responses between the LED and placebo applications will be analyzed. The therapeutic effects of LED could minimize muscle fatigue in patients with COPD by increasing exercise tolerance.

**Trial registration:**

Trial registration number:
NCT01448564

## Background

Chronic obstructive pulmonary disease (COPD) primarily affects the lungs, but it is a systemic disease with several extra-pulmonary manifestations, most notably peripheral muscle dysfunction [1].

Skeletal muscle dysfunction in patients with COPD is characterized by a reduction of muscle strength [2] and endurance [3]. There is also a redistribution of muscle fiber types (low proportion of oxidative fibers and high proportion of glycolytic fibers) [4,5], changes in the bioenergetics (decrease of aerobic capacity, predominance of glycolytic metabolism and rapid accumulation of lactate) [6] and reduction of the capillary density and capillary/fiber ratio [7,8]. These alterations, alone or combined, are responsible for early muscle fatigue in COPD patients.

Since peripheral muscle dysfunction is one of the most serious systemic effects of COPD, strategies for improving muscle function are a priority in scientific research. In this context, phototherapy is an electrophysical intervention to be considered to prevent or postpone muscle fatigue in COPD due its effects, such as vasodilation, recruitment of collateral circulation, increased supply of oxygen and mitochondrial ATP level in the muscle [9].

Phototherapy by low-intensity laser and light-emitting diodes (LED) is a non-thermal therapy [10] characterized by a coherent and non-coherent beam of light, respectively [11]. It has been shown that both the laser and LED therapy produce similar effects due to the absorption of photons by chromophores in their tissue specific wavelengths. Currently, the LED has been presented as an alternative to the therapies that use low-intensity laser due to its low cost and smaller size [12].

The effects of phototherapy promoted by LED are mediated by the phenomenon of biostimulation [13]. In brief words, biostimulation can be explained by the absorption of energy by the intracellular chromophores [14]. The light energy is converted into chemical energy affecting positively several cellular biochemical processes [10,14].

Skeletal muscle, a tissue with a high rate of aerobic metabolism, is highly responsive to the stimulating effects of phototherapy through infrared and red rays [15]. Among the acute effects of the LED, the prevention of muscular fatigue [16] and reduced levels of lactate [17] stand out. Additionally, improvement in exercise performance and attenuation of inflammatory biochemical markers (creatine kinase, CK) and C-reactive protein (CRP) [18] have been observed. In this context, this study will investigate whether the positive effects, previously demonstrated in healthy individuals and athletes, might occur in patients with COPD. Our hypothesis is that the therapeutic effects of LED as vasodilation, improves the collateral circulation, increasing the level of oxygen content in tissues, and increased levels of mitochondrial ATP [19] could minimize muscle fatigue, increasing exercise tolerance in patients with COPD.

The primary aim of this study is to investigate the acute effects of LED phototherapy on muscle function, exercise capacity and cardiorespiratory responses during isometric (60% of maximum voluntary contraction) and dynamic (maximal incremental cycle ergometer test) exercises in patients with COPD. The secondary goal is to assess the effects of LED phototherapy on biochemical markers (CK, CRP and lactic acid).

## Methods/Design

### Study design

This study is a crossover, double blind (patient and evaluator) and randomized trial. Randomization will be performed to determine whether the patient will receive LED or placebo (Figure 1). This study will be conducted in the Exercise Physiology Laboratory at the Nove de Julho University. This study was approved by the Ethics Committee of our institution (11/451953) and registered in Clinical Trials.gov NCT01448564 (2011-OCT-06).

**Figure 1 F1:**
[figure not shown]
Flow of patients through the study.

The study will assess 35 patients with moderate to severe obstruction (forced expiratory volume**-**one second (FEV_1_) ≤70% predicted) and stable disease suggested by the absence of any change in medication and symptoms (increasing cough, increasing sputum volume and worsening sputum purulence) in the four weeks before the study. The exclusion criteria are oxygen-dependent patients, patients with orthopedic or neuromuscular disorders, and dark-skinned patients. Dark-skinned patients will be excluded because their greater epidermal melanin content acts as competing chromophores. This protocol was approved by the institutional ethics committee and all patients will sign a written informed consent before their participation in the study.

### Outcome measures

The primary outcome for muscle function will be the endurance time (sec) on cycling. The secondary outcomes will be the slope coefficient from the regression line between the median frequency and endurance time, fatigue and dyspnea scores (from 0 to 10), and the levels of CK (U/L), CRP (mg/dl) and lactate (mmol/L). In addition, for the dynamic protocol, the maximum workload (watts), VO_2_ peak (L), ventilation (L), and heart rate (bpm) variables will also be analyzed.

### Assessment

#### Spirometry

Spirometry will be used to classify the severity of the obstruction and it will be performed at each visit before the tests to ensure similar pulmonary function on the different days. The tests will be performed using the CPF-System (Medical Graphics Corporation®, St. Paul, MN, USA) after administering a bronchodilator (400 μg of inhaled salbutamol). The technical procedures, acceptability and reproducibility criteria will follow the recommendations of the Brazilian spirometry consensus [20]. Values of forced vital capacity and forced expiratory volume in the first secondwill be compared with those predicted for the Brazilian population. The following variables were recorded: FVC, FEV_1_, FEV_1_/FVC. The data were expressed in absolute values (liters) and in percentage of predicted (%) No, the correct sentence is like that (percentage of predict)[21]. This test will take approximately 20 minutes.

#### Skeletal muscle function assessment

The strength of the quadriceps femoris will be obtained from the dominant leg by the maximal isometric voluntary contraction (MIVC). This measurement will be made with the patients seated on a leg extension chair (Carci®, São Paulo, Brazil) at 60° of knee flexion. A non-elastic strap connecting the ankle to a load cell (EMG System EMG800C, São José dos Campos, Brazil) will be interfaced to a computer to record the MIVC. The force will be expressed in Kgf. A strap will be placed across the patient’s pelvis to minimize hip movement during the tests. The patients will perform three repetitions of MIVC of the knee extensors, each one maintained for five seconds, with a one minute rest between them. The highest value from the three reproducible contractions (<5% variability among attempts) will be considered for analysis, when the difference in strength of three contractions exceeds 5%, another measure of MIVC will be requested. The greatest value of these three contractions will be considered as the MIVC [22]. After a resting period of five minutes, the IET of the quadriceps femoris will be evaluated by the isometric endurance time at 60% of the MIVC until the limit of tolerance (Tlim). The isometric endurance test will be finished when a 20% drop of the produced force occurs. All measurements will be performed with visual feedback on the computer screen [22]. Dyspnea and leg fatigue will be evaluated before and immediately after the test by the modified Borg scale [23]. This test will take approximately 15 minutes.

#### Surface electromyography recording

Surface electromyography (sEMG) signals will be recorded (EMG System, model EMG800C, Sao José dos Campos, Brazil) during the MIVC, isometric endurance test, and the incremental cycle ergometer test. The sEMG signals will be recorded with a preamplifier (gain 1,000x) and common mode rejection of more than −85 dB. The participants’ skin will be prepared before the placement of the EMG electrodes by shaving the hair at the site of the electrode placement and cleaning the skin with alcohol [24].

Bipolar passive disposable dual Ag/AgCl snap electrodes with a 1-cm diameter for each circular conductive area and a 2-cm center-to-center spacing will be placed over the longitudinal axes of the vastuslateralis. They will be placed in the direction of the muscle fiber, taking as reference two-thirds of the distance between the anterior superior iliac spine and the lateral edge of the patella [24]. Finally, a ground electrode will be put on the left elbow.

The sampling frequency will be 2,000 Hz [25] and the criterion adopted to normalize the EMG data will be the MIVC. The digitized EMG data will first be band-pass filtered at 20 to 400 Hz using a fourth order Butterworth filter with a zero lag. For the temporal analysis, the amplitude of the EMG signals will be expressed as root mean square (RMS) (1-s moving window) and normalized by MIVC [26]. For the time-frequency analysis, the EMG data will be analyzed with a short-time Fourier transform applied to 1-s epochs [27]. The median frequency of the spectrum for each epoch will be computed, and the linear regression of the median frequencies versus time will be determined. The slope of the straight line (indicating the rate of frequency change per second) will be adopted as a second index of fatigue [28-30]. All data were analyzed using a customized program written in Matlab (Mathworks Inc., Torrance, California, EUA).

#### Cardiopulmonary exercise testing

The maximal incremental cycle ergometer test will be carried out on an electromagnetically braked cycle ergometer (Corival, LODE B.V. Medical Technology, Groningen, The Netherlands) with gas exchange and ventilatory variables being analyzed breath-by-breath (Medical Graphics Corporation (MGC), St. Paul, MN, USA). After 2 minutes at rest and more than 2 minutes with a real “zero” workload obtained by a system that moves the ergometer flywheel, the power (W) will be continuously increased in a linear “ramp” pattern (5 to 15 W min^-1^) so that the incremental exercise test duration will be between 8 and 12 minutes [29]. The following data will be obtained breath-by-breath: pulmonary oxygen uptake (VO_2_, mL min^-1^), pulmonary carbon dioxide production (VCO_2_, mL min^-1^), minute ventilation (VE, L min^-1^), tidal volume (VT, mL), respiratory rate (f, respirations per minute); ventilatory equivalent for O_2_ and CO_2_ (VE/VO_2_ and VE/VCO_2,_ respectively), and end tidal partial pressures of O_2_ and CO_2_ (PETO_2_ and PETCO_2_, mmHg). ECG tracings and heart rate (HR) will be recorded continuously and oxygen pulse (VO_2_/HR) will be calculated. Arterial oxygen saturation (SpO_2_) will be measured by pulse oximetry. Blood pressure (BP) will be measured during every two minutes of exercise. The average VO_2_ for the last 15 s of the ramp will be considered representative of the subject’s peak VO_2_. Subjects will be asked to rate dyspnea and leg fatigue at exercise cessation by using the modified Borg scale [23]. This test will take approximately 30 minutes.

#### Dynamic endurance testing

For the dynamic endurance test (DET), the same procedures described above will be followed, except with 75% of the maximal workload obtained from incremental cycle ergometer test used instead of the IET. Patients will perform this test until the limit of tolerance (Tlim).

#### Venous blood

Blood samples will be collected to measure the lactate levels, as well as the activity of CK and CRP. To measure these settings, a qualified nurse (blind to the group allocation) will perform the asepsis of ventral side of the arm. A blood sample will be collected prior to the application of the LED or placebo and immediately after ending the isometric endurance testing (Visits 1 and 2). The same procedure will be performed at Visits 3 and 4 prior to the application of the LED or placebo and after the cycle ergometer testing. The samples will be analyzed with infrared spectrophotometry via a spectrophotometer (FEMTO® Industry and Trade of Instruments, São Paulo, SP, Brazil) and specific kits for blood lactate analysis (Bioclin®, Belo Horizonte, Brazil) and CK analysis (Labtest®, Lagoa Santa, Brazil). PCR analysis will be carried out by the agglutination method using a specific analysis kit (Wiener Laboratories®, Rosario, Argentina).

#### LED

Patients will receive a single application of LED or placebo on different days (a week apart). The LED or placebo will be administered immediately before the isometric and dynamic protocols. The radiation will be held stationary with slight pressure of the LED cluster (THOR Photomedicine®, London, UK) in contact with skin at an angle of 90°. The application will be performed on two points along the ventral side of the rectus femoris [31], one point on the greater prominence of the muscle belly of the vastuslateralis and vastusmedialis muscles. For the isometric exercise protocol, the application will be performed only on the right quadriceps femoris, while for the dynamic exercise protocol, both lower limbs will receive the application on the four sites for the quadriceps femoris, two sites for the hamstring muscle belly, and one site in the center of the triceps surae [18]. Each point will be irradiated for 30 s. The energy received at each point will be 41.7 J. The irradiation settings are summarized in Table 1.

**Table 1 T1:** Settings for LED cluster

Number of LEDs	69 (34 red LEDs and 35 infrared LEDs)
Wavelength	660 nm (red) and 850 nm (infrared)
Frequency	Continuous output
Optical output	10 mW (red) and 30 mW (infrared)
LED spot size	0.2 cm^2^ (for both), total spot sizes 13.8 cm^2^
Power density	0.05 W cm^-2^ (red) and 0.15 W cm^-2^ (infrared)
Energy	41.7 J (0.3 J from each red LED and 0.9 J from each infrared LED)
Energy density	1.5 J cm^-2^ (red) and 4.5 J cm^-2^ (infrared)
Treatment time	30 s per point, 120 s (total treatment time for isometric test), 420 s (total treatment time for dynamic test)
Number of irradiation points per muscle	4 points (isometric test) and 14 points (dynamic test)
Total energy delivered	166.8 J (isometric test), 583.8 J (dynamic test)
Application mode	Cluster held stationary to skin with slight pressure at a 90° angle

For the placebo, the same procedures will be performed but without irradiation. During the application of the LED or placebo, the patient will use protective glasses that make it impossible to see whether there is light being irradiated. This test will take approximately five minutes.

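### The isometric protocol takes strength from the dominant leg but applies LED or placebo to the right leg, so a left-dominant patient would be tested on a muscle that is never irradiated

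*Protocol article*

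**What the plan says.** Skeletal muscle function assessment names the leg for the strength measurement: "The strength of the quadriceps femoris will be obtained from the dominant leg by the maximal isometric voluntary contraction (MIVC"). After a five-minute rest, "the IET of the quadriceps femoris will be evaluated by the isometric endurance time at 60% of the MIVC". That sentence names no side. Its load is a percentage of the dominant-leg value, and the paragraph mentions no other leg.

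The LED section names the treated leg for the isometric protocol: "the application will be performed only on the right quadriceps femoris". For the dynamic protocol, by contrast, "both lower limbs will receive the application on the four sites for the quadriceps femoris", with further sites on the hamstrings and calf.

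Table 1 gives the number of irradiation points as "4 points (isometric test) and 14 points (dynamic test") and the total energy as "166.8 J (isometric test), 583.8 J (dynamic test").

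Eligibility is set out under Study design: "The exclusion criteria are oxygen-dependent patients, patients with orthopedic or neuromuscular disorders, and dark-skinned patients". Leg dominance does not appear there. The Protocol section and Surface electromyography recording name no side for the tested muscle.

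**The concern.** One section identifies a leg by dominance and the other by side. The two rules pick the same leg only in right-dominant patients, and left-dominant patients are eligible. In such a patient the right quadriceps would receive LED or placebo and the left quadriceps would then be tested, at both isometric visits. The crossover does not repair this, because the mismatch is the same in both periods.

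The article's rationale is largely local. The Discussion attributes delayed fatigue, with some caution, to local action, and dark-skinned patients are excluded because melanin in the skin competes for the light. If the effect is local, a left-dominant patient contributes no LED-placebo contrast to the isometric results, and the comparison is pulled towards no difference. That concerns isometric endurance time, the EMG median-frequency slope and RMS, leg-fatigue scores and the blood markers taken around that test. The stated primary aim covers isometric as well as dynamic exercise, and two of the four endurance visits are given to the isometric test. A null isometric result would be hard to interpret.

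**Working it through.** **1. Does Table 1 confirm that only one quadriceps is treated?** Inputs are from the LED section and Table 1: 34 red LEDs at 0.3 J, 35 infrared LEDs at 0.9 J, 30 s per point.

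- Energy per point: 34 × 0.3 + 35 × 0.9 = 10.2 + 31.5 = 41.7 J, as stated.
- Isometric: 4 × 41.7 = 166.8 J and 4 × 30 = 120 s, as stated.
- Dynamic: (4 + 2 + 1) sites × 2 limbs = 14 points; 14 × 41.7 = 583.8 J and 14 × 30 = 420 s, as stated.
- If both quadriceps were treated in the isometric protocol: 8 points and 8 × 41.7 = 333.6 J, which is not what the table gives.

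The table reproduces exactly and rules out bilateral treatment before the isometric test.

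**2. Which leg is tested and which is treated?**

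| Patient | MIVC leg (stated) | Isometric endurance leg (inferred) | Treated leg (stated) | Tested muscle irradiated? |
|---|---|---|---|---|
| Right-dominant | right | right | right | at the LED visit |
| Left-dominant | left | left | right | at neither visit |

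**3. How large could the dilution be?** The planned number is N = 35 (Statistical analysis). The share p of left-dominant patients is not in the article; 5% to 20% is an assumption. If the effect is purely local:

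- expected number affected = N × p;
- probability of at least one = 1 − (1 − p)^N;
- mean isometric effect is multiplied by (1 − p);
- sample size for the same power is multiplied by about 1/(1 − p)², holding the SD of the differences fixed.

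| p (assumed) | Expected patients of 35 | P(at least one) | Effect multiplier | Sample-size multiplier |
|---|---|---|---|---|
| 5% | 1.75 | 0.83 | 0.95 | 1.11 |
| 10% | 3.5 | 0.97 | 0.90 | 1.23 |
| 20% | 7 | > 0.999 | 0.80 | 1.56 |

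The Abstract gives 30 patients instead of 35. With 30 the expected number is 1.5 to 6, and the effect multipliers do not change.

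**4. Is the primary comparison touched?** Outcome measures names endurance time on cycling as primary, and Statistical analysis bases the sample size on a 55 s difference in the dynamic test. Both legs are treated before that test, so leg dominance plays no part in it.

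**The case against.** The strongest reply is that this is loose wording. The side is attached only to the strength measurement; the sentences on the endurance test, the EMG electrodes and the visit schedule name none. The word right may be shorthand for the tested leg, and staff are unlikely to treat one leg and test the other minutes later. The schematic figure of the protocol could not be read here and may show the side.

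Part of this stands. That the endurance test uses the dominant leg is an inference, though a close one, because the load is set from that leg's MIVC. But reading the endurance test as always on the right leg does not remove the problem: in a left-dominant patient the load would then come from the other leg's strength, and 60% would no longer describe the tested muscle. Either way the two sections need to agree.

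Three stronger readings are tempting, and the article does not support them.

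- A reader might infer that the trial's main comparison is compromised. It is not: the primary outcome and the sample size belong to the dynamic protocol.
- A reader might infer that a left-dominant patient's two isometric visits amount to two placebo visits, with a true difference of exactly zero. That holds only for a purely local effect. The Discussion calls local action probable, and it also mentions release of substances such as histamine and bradykinin and spread to surrounding tissue, so some non-local effect is not ruled out.
- A reader might take 5% to 20% as an estimate. It is an assumed range; the article offers no figure.

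It is also fair to say that the expected bias is towards no difference. The cost is lost sensitivity in the isometric results, with no added risk of a false positive.

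**Conclusion.** The inconsistency is real and wrong as written: two specific rules, both in the current text, cannot give a matched isometric comparison in every eligible patient. It is confined to the isometric protocol. To the extent that the effect is local, the mean isometric effect shrinks by a factor (1 − p), which is 0.95 to 0.80 for an assumed p of 5% to 20%, or about 2 to 7 of 35 patients. The conclusion rests on three conditions: the endurance test is done on the leg used for MIVC, left-dominant patients enrol, and staff follow both sections literally. The size is unknown from the article. The need to reconcile the text does not depend on it, since even at 5% the chance of enrolling at least one such patient is 0.83.

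**What to change.** Reconcile Skeletal muscle function assessment with the LED section so that MIVC, isometric endurance, EMG and the LED or placebo application all refer to one leg, identified by the same rule in both sections and kept the same for each patient across both isometric visits. Which leg that is, and how it is defined, is for the investigators. Surface electromyography recording and the Protocol section should use the same term.

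The cost is a few words. It adds no visit, procedure or patient, and the point counts, times and energies in Table 1 stay as they are because one quadriceps is still treated. Trial status says recruitment had not opened, so the change can be made before any data are affected; analysis afterwards could not recover a contrast that was never applied to the tested muscle.
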